### 2.2. Inclusion Criteria

Patients diagnosed with asthma, age older than 20 years and less than 75 years, with BMI greater than 25 kg/m^2^ will be included. All patients must have experienced one or more episodes of moderate or severe exacerbations in the previous year. Written informed consent for participation in the present study will be obtained from all patients.

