### 2.4. Study Endpoints

The primary endpoint is reduction in the exacerbation rate after 48-week treatment with azithromycin compared to that before the intervention (Table 1). The asthma exacerbation rate is defined as the proportion of analyzed cases with asthma exacerbations after treatment. Secondary endpoints are differences in clinical and laboratory parameters between before and after azithromycin treatment, including the blood eosinophil ratio, eosinophil count, IgE, pulmonary functions such as vital capacity (VC), forced vital capacity (FVC), %VC, forced expiratory volume in one second (FEV_1_), FEV_1_%, and %FEV_1_, and weight, BMI, level of fractional exhaled nitric oxide (FeNO), and scores on the asthma control test. Other secondary endpoints are to clarify the characteristics of the frequency of asthma exacerbations in improving/non-improving patients, and the diversity indices of the gut microbiome including the Chao 1, Shannon, and Simpson indices. For other exploratory endpoints, height, weight, BMI, and the tendency for decreased exacerbations will be assessed at 24 weeks of azithromycin treatment. In addition, biomarkers including cytokines, chemokines, short-chain fatty acids, metabolomics, and species of the gut microbiome will be compared between before and after azithromycin treatment and examined for relationships between changes and exacerbation at 48 weeks. The effects of sex and age attenuating the effect of azithromycin on exacerbations will also be assessed, because sex and age have been shown to have great impacts on the incidence and pathophysiology of asthma and obesity [26,48,49,50].

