### 2.6. Sample Size

A previous study reported that the incidence rate ratio of asthma exacerbations for azithromycin compared to placebo was approximately 0.6 [36], but the current participants have obesity, which is estimated to reduce the attenuation effect due to the pharmacological differences between lean and obese individuals [51,52]. Thus, we anticipate an incidence rate ratio of 0.9 with azithromycin and set the expected exacerbation rate after intervention at 90%, with the exacerbation rate before the intervention set at 100%. Based on the normal approximation of the binomial distribution with a significance level of 5% and power of 90%, 44 patients are required. Thus, the target sample size was set at 50 patients considering dropouts.

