### 2.8. Statistical Analysis

The primary and secondary endpoints and safety will be assessed in all patients completing 48 weeks of treatment. Then, patients without necessary exacerbation data for analysis or who withdrew consent before treatment will be excluded. For the primary endpoint, the asthma exacerbation rate at 48 weeks and its two-sided 95% confidence interval (CI) will be estimated with the normal approximation. The asthma exacerbation rate difference between pre- and post-treatment will also be tested binomially. For the clinical laboratory parameters and the diversity indices of the gut microbiome at pre-treatment and post-treatment as secondary endpoints, paired *t*-tests or McNemar’s tests will be used. The chi-squared test will be used to investigate the characteristics related to the frequency of asthma exacerbations. For other exploratory endpoints, height, weight, BMI, and tendency for an attenuation of the exacerbation rate at 24 weeks will be assessed by paired *t*-tests. Univariate analysis and multivariate analysis with a logistic regression model, adjusting BMI and body weight, will be performed to evaluate the relationships between the changes (improvement or no improvement in biomarker changes) and asthma exacerbation at 48 weeks.

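### The exploratory 24-week exacerbation rate is a yes/no outcome with a baseline of yes for every patient, yet it is assigned a paired t-test rather than the binomial method named for week 48 (minor).

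*Protocol article*

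**What the plan says.** The protocol article, section 2.4 (Study Endpoints), gives one definition of the outcome: "The asthma exacerbation rate is defined as the proportion of analyzed cases with asthma exacerbations after treatment". It then lists a tendency towards fewer exacerbations at 24 weeks among the exploratory endpoints.

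The baseline is fixed in two places. Section 2.2 (Inclusion Criteria) states: "All patients must have experienced one or more episodes of moderate or severe exacerbations in the previous year". Section 2.6 (Sample Size) plans "with the exacerbation rate before the intervention set at 100" per cent.

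Section 2.8 (Statistical Analysis) names two methods for the rate:

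- Week 48 (primary): a two-sided 95% interval by the normal approximation, and "The asthma exacerbation rate difference between pre- and post-treatment will also be tested binomially". Neither the null value nor the form of the test (exact or approximate) is given.
- Week 24 (exploratory): "tendency for an attenuation of the exacerbation rate at 24 weeks will be assessed by paired *t*-tests", in one list with height, weight and BMI.

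McNemar's test also appears in section 2.8, but only for the laboratory parameters and the microbiome diversity indices.

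**The concern.** A paired t-test is meant for within-patient differences on a measured scale. Height, weight and BMI qualify. A proportion of patients with an event does not, because each patient contributes 0 or 1. Here the before value is also the same for everyone, so there is no pairing left to exploit.

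Week 24 reports the same quantity as the primary endpoint at an earlier time, and readers will set the two side by side. If the methods differ, the same number of exacerbation-free patients could be called significant at one time point and not at the other for no reason other than the change of test.

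**Working it through.** **Inputs.** Outcome: proportion of patients with an exacerbation (section 2.4). Baseline: yes for all (sections 2.2 and 2.6). Number analysed: n = 44 required, 50 targeted (section 2.6). The article states no figure for the week-24 test, so there is none to reproduce; 44 and 50 serve here only as sample sizes.

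**Step 1: what the paired t-test becomes.** Let k of n patients be exacerbation-free by week 24. The paired difference is 1 for those k and 0 for the rest. Its mean is k/n and its sample variance is k(n−k)/[n(n−1)], so

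t = √[k(n−1)/(n−k)], with n−1 degrees of freedom.

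At k = 0 the variance is zero and t is undefined. Example at n = 44, k = 4: t = √(4×43/40) = 2.07, p = 0.044.

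**Step 2: candidate tests for the same data.**

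- Exact binomial against 100%: under the null no patient can be exacerbation-free, so any k ≥ 1 gives p = 0.
- Normal approximation with the estimated variance (Wald): z = √[kn/(n−k)].
- Exact sign test (exact McNemar, all discordant pairs in one direction): p = min(1, 2×0.5^k). The plan does not assign this to exacerbations; it is shown for reference only.

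Two-sided p-values at n = 44:

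| k | Paired t | Wald | Exact binomial vs 100% | Exact sign/McNemar |
|---|---|---|---|---|
| 1 | 0.323 | 0.312 | 0 | 1.00 |
| 2 | 0.160 | 0.148 | 0 | 0.50 |
| 3 | 0.083 | 0.073 | 0 | 0.25 |
| 4 | 0.044 | 0.036 | 0 | 0.125 |
| 5 | 0.024 | 0.018 | 0 | 0.063 |
| 6 | 0.013 | 0.008 | 0 | 0.031 |

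At the 5% level the t-test rejects from k = 4, the Wald test also from k = 4, the exact binomial test from k = 1 and the exact sign test from k = 6. At n = 50 the pattern is the same (paired t at k = 4: p = 0.044).

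**Step 3: how likely is a small k at week 24?** The article gives no week-24 event rate, so these are assumptions.

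- Section 2.6 has "set the expected exacerbation rate after intervention at 90" per cent. If that held already at week 24, k would average 0.1×44 = 4.4. The t-test and the exact binomial test would differ (k = 1 to 3) with probability 34%, or 25% at n = 50.
- If instead 90% is reached at 48 weeks under a constant hazard common to all patients, the event-free fraction at 24 weeks is √0.1 = 0.316. Then k averages 0.316×44 = 13.9, and the probability of k ≤ 5 is about 0.2%.
- With Poisson rates of 1 to 2 events per year and no drug effect, exp(−rate×24/52) gives 63% to 40% event-free, or k of about 28 to 17.

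In the last two cases every version rejects.

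**Step 4: the interval used at week 48.** Near 100% the normal approximation also behaves poorly. With 3 of 44 exacerbation-free the proportion is 41/44 = 0.932, its standard error is √(0.932×0.068/44) = 0.038, and the upper limit is 0.932 + 1.96×0.038 = 1.006, above 100%. Carrying that interval over to week 24 would therefore not be a good repair.

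**The case against.** A reader might infer that the week-24 test contradicts the week-48 test. The article does not support that. Its statement on the week-48 test fixes neither the null nor an exact form, and the only binomial form it names elsewhere, for the sample size and the interval, is the normal approximation. A Wald test of that kind agrees with the t-test at the 5% level for every k from 1 to 10. The comparison with McNemar's test is likewise no conflict within the plan, since McNemar's test is not assigned to exacerbations at either time point. And small k is unlikely at week 24, because fewer patients will have had an event in half the follow-up. These points stand, and they limit the impact.

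A second objection is that counts per patient may be meant. The week-24 item in section 2.4 speaks of fewer exacerbations, section 2.5 collects the number in the previous year, and section 2.6 starts from an incidence rate ratio. For counts, a paired t-test is a defensible exploratory choice. This is possible, but section 2.8 uses the term exacerbation rate, whose only definition is a proportion, and no count endpoint is defined for week 24. If counts were intended, the sentence still has to say so.

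The objection does not remove the core: a method is stated, and it does not fit the outcome as defined.

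**Conclusion.** The point holds as a minor one. As written, the 24-week analysis is a one-sample t-test on 0/1 data, undefined when no patient is exacerbation-free, and not the method named for the same quantity at week 48. It can give a different verdict from an exact test when few patients are exacerbation-free (at n = 44, k = 1 to 3 against an exact binomial test of 100%). It does not differ from a normal-approximation test, and from k = 6 all versions considered reject.

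This rests on reading the week-24 rate by the definition in section 2.4 and on analysing about 44 to 50 patients. How often the choice would matter depends on an unstated week-24 event rate: about one time in three at n = 44 if 90% already applied at week 24, close to never under the other assumptions shown. The endpoint is exploratory, so neither the primary conclusion nor the sample size depends on it.

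No choice of test repairs the comparison of a 24-week window with a one-year baseline that is 100% by selection. That is a further reason to report week 24 descriptively.

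**What to change.** In section 2.8:

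- Keep paired t-tests at 24 weeks for height, weight and BMI only.
- For exacerbations by week 24, report the number and proportion of patients with an event and a Wilson or exact 95% interval, and drop the t-test.
- Use that same interval for the week-48 rate in place of the normal approximation, so that the two time points can be read together.
- If counts per patient were meant at week 24, say so, define the count, and compare it over look-back periods of equal length before and after the start of treatment.

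The cost is a sentence or two of text. The proportion-based version needs no new data, visits or patients. The count version would need the previous year's exacerbations to be dated closely enough to form a matching period.

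### The biomarker logistic regression sets a two-category predictor against an outcome with only four or five exacerbation-free patients expected, so it has little power and often gives no finite odds ratio

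*Protocol article*

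**What the plan says.** Section 2.8 (Statistical Analysis) of the protocol article states: "Univariate analysis and multivariate analysis with a logistic regression model, adjusting BMI and body weight, will be performed". The relationship examined is between "the changes (improvement or no improvement in biomarker changes) and asthma exacerbation at 48 weeks". Biomarker change therefore enters as a two-category predictor, with BMI and weight as adjustment terms.

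Section 2.4 makes the outcome yes/no per patient: "The asthma exacerbation rate is defined as the proportion of analyzed cases with asthma exacerbations after treatment". Section 2.2 fixes the baseline at 100% by eligibility: "All patients must have experienced one or more episodes of moderate or severe exacerbations in the previous year".

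For the post-treatment rate, section 2.6 says the investigators "set the expected exacerbation rate after intervention at 90%, with the exacerbation rate before the intervention set at 100" per cent. It continues: "Based on the normal approximation of the binomial distribution with a significance level of 5% and power of 90%, 44 patients are required", and "the target sample size was set at 50 patients considering dropouts". Section 2.8 analyses completers of the 48 weeks, so about 44 and at most about 50 patients are planned for.

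Section 2.1 defines BMI in the usual way, as weight over height squared. Section 2.4 lists the biomarker-exacerbation relationships among the exploratory endpoints. The abstract, introduction and conclusions name the search for biomarkers correlated with fewer exacerbations as a purpose of the study.

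**The concern.** In a logistic model the information is limited by the smaller outcome class. Here that class is the exacerbation-free patients, and the design expects very few of them. A two-category predictor makes this worse. If all the exacerbation-free patients fall on one side of the improved/not improved cut, the 2×2 table has an empty cell and the maximum-likelihood odds ratio is zero or infinite. If they do not, the odds ratio rests on two or three patients per cell.

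At stake is whether the stated route from biomarkers to clinical benefit can show anything. The introduction defends the single-arm design partly because it allows biomarkers tied to outcome to be explored in a small sample. The model would be repeated over cytokines, chemokines, short-chain fatty acids, metabolites and microbial species. A real association could easily be missed, and a null result could be misread as evidence of none.

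**Working it through.** **Inputs from the protocol article.** Post-treatment rate 90% (2.6); N = 44 required and 50 targeted (2.6); binary outcome (2.4); binary biomarker change plus BMI and weight, so three slopes (2.8).

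**Assumed, not in the documents.** Share of improvers 50% or 30%; height SD 0.08 m, giving a BMI-weight correlation of about 0.72; no true effect unless stated.

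**The plan's own figure.** N = 44 does not reproduce from 100% versus 90%, 5% significance and 90% power. The one-sample normal approximation with null variance gives 15 (24 with continuity correction). With the alternative variance it gives 78 one-sided or 95 two-sided. That is a separate matter: 44 and 50 are used below only as planned numbers of patients.

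**1. Size of the smaller class.**
- 44 × 0.10 = 4.4 and 50 × 0.10 = 5.0; the central 95% binomial range is 1 to 9 for both.
- Probability of at most two exacerbation-free patients: 17% at N = 44, 11% at N = 50.
- Per slope: 4.4/3 = 1.5 and 5.0/3 = 1.7.

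**2. Chance of no finite odds ratio, by hand.** Let q be the share of improvers. The chance that either biomarker group has no exacerbation-free patient is (1 − 0.1q)^N + (1 − 0.1(1 − q))^N − 0.9^N.
- N = 44, q = 0.5: 2 × 0.95^44 − 0.9^44 = 0.209 − 0.010 = 20%.
- N = 44, q = 0.3: 0.97^44 + 0.93^44 − 0.9^44 = 0.262 + 0.041 − 0.010 = 29%.
- N = 50, q = 0.5: 0.154 − 0.005 = 15%.
- N = 50, q = 0.3: 0.218 + 0.027 − 0.005 = 24%.

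Simulation of the full three-slope model (600 trials per setting, separation detected by linear programming) gives 21% and 32% at N = 44, and 15% and 25% at N = 50.

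**3. Precision where the fit exists.** With average cell sizes at N = 44 and q = 0.5, the unadjusted SE of the log odds ratio is √(2/2.2 + 2/19.8) = √1.010 = 1.00. The ratio of upper to lower 95% limit is exp(2 × 1.96 × SE), here about 51.

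| N | Median SE, adjusted model (simulated) | Upper/lower 95% limit |
|---|---|---|
| 44 | 1.15 to 1.21 | about 90 to 113 |
| 50 | 1.05 to 1.14 | about 60 to 89 |

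**4. Role of the covariates** (N = 44, 90%, q = 0.5, 3,000 runs).

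| Model | No finite odds ratio | Median SE (biomarker) |
|---|---|---|
| Unadjusted | 19.8% | 1.05 |
| BMI only | 19.9% | 1.09 |
| BMI and weight | 20.3% | 1.15 |

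**5. Behaviour of the test.** In the same null simulation the Wald test for the biomarker rejects in 0.6% of trials at N = 44 and 0.8% at N = 50, far below 5%.

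**6. Sensitivity to the rate** (N = 44).
- 80%: 8.8 exacerbation-free; 1% to 6% not estimable; interval ratio about 28 to 35.
- 70%: 13.2 exacerbation-free; 0.2% not estimable with no effect, about 3% with a true effect; median SE 0.72, so exp(3.92 × 0.72) = about 17.
- 60%: 17.6 exacerbation-free; at most 1% not estimable; interval ratio about 14 to 18.

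**7. Effect of the fix.** Assume a log odds ratio of 1 per SD of biomarker change, N = 44 and 90%. The planned coding leaves 43% of fits not estimable, with power of about 3%. Continuous change with Firth penalisation leaves about 0% not estimable, with power of about 29%.

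**The case against.** The best defence has four parts.

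- **The 90% is deliberately cautious.** Section 2.6 moves a cited ratio of about 0.6 to 0.9. This stands in part. Non-estimability is confined to rates near the planning value, but imprecision remains at lower rates: the interval is still about 17-fold at 70%.
- **The analysis is exploratory.** This stands. No primary or secondary endpoint depends on the model, and the paired before/after biomarker comparisons are untouched.
- **Details belong in a SAP that is not shown.** This stands for the handling of separation, log scaling and multiplicity, whose absence here is no fault. It does not cover the two-category coding, the yes/no outcome or the covariates, which the article itself specifies.
- **BMI and weight are not the cause.** This stands. A reader may infer that their collinearity breaks the model, since weight given BMI adds only height. But collinearity between two adjustment terms mainly inflates their own standard errors. Removing weight lowers the biomarker's median SE only from 1.15 to 1.09 and leaves estimability almost unchanged.

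A reader may also infer that any positive findings would be noise. The calculation shows the opposite tendency for a single test: far fewer false positives than the nominal 5%. Nor does every fit fail. On the planning assumptions, most give a finite odds ratio, though a very imprecise one.

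**Conclusion.** The point holds as a modest but real weakness of an exploratory analysis that carries a declared aim. If the 90% rate is right, the binary predictor against so sparse an outcome gives no finite odds ratio in about 15% to 32% of fits per biomarker, and intervals of about 60- to 113-fold in a typical remaining one. The harm is lost power. These figures rest on the protocol's rate and numbers, on an assumed 30% to 50% of improvers, and on no true effect. With a true effect, separation is more frequent (43% in the case examined). Adjustment for both BMI and weight adds little and costs a degree of freedom, but is secondary. The primary conclusion is unaffected.

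**What to change.** In section 2.8, or in the SAP before analysis:

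1. Replace improved/not improved by continuous biomarker change, on the log scale where skewed, adjusted for its baseline value.
2. Fit by Firth penalised logistic regression.
3. Keep BMI alone as the body-size covariate. The degree of freedom released is then used by the baseline value.
4. Give odds ratios per unit or per SD with intervals, report them as exploratory, and do not read a non-significant result as absence of association.

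A count model for exacerbations over 48 weeks may be added as a supportive analysis. It answers a different question from the proportion defined in section 2.4 and should not replace it.

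The cost is analysis wording and code. Biomarkers are already measured before treatment and at week 48 (section 2.5), so no new data are needed. The fix does not make the study large: power of about 29% in the assumed case is still low. For 5 to 10 exacerbation-free patients per slope, a conventional target assumed here, three slopes at a 10% exacerbation-free rate would need 3 × 5/0.10 = 150 to 3 × 10/0.10 = 300 patients.

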## 3. Discussion

The present study focuses on asthma with obesity, which is one of the important forms of severe asthma [22], and this phenotype does not have effective treatments. Azithromycin, the intervention drug in the present study, is widely and continuously used for patients with non-tuberculosis mycobacterial infections [43], which guarantees its safety in terms of adverse effects. In addition, azithromycin has already been reported to have an attenuating effect on exacerbations in asthma patients regardless of their BMI [36], and, notably, it has the capacity to alter the gut microbiome as an antibiotic [37,38]. Thus, the present study will allow us to evaluate the attenuating effect on exacerbations, especially in asthma patients with obesity, and explore biomarkers, targeting molecules including the gut microbiome that have been correlated with decreased exacerbations. This is the first prospective intervention study to explore an effective drug for obesity-induced severe asthma focusing on the gut microbiome.

The gut microbiome is increasingly recognized as a mechanistic basis of obesity-associated conditions, including asthma. For example, the prevalence and pathophysiology of type 2 diabetes mellitus, metabolic syndrome, non-alcoholic fatty liver disease, and cardiovascular disease are associated with the gut microbiome [54,55,56]. Even in obesity itself, the gut microbiome has a huge impact, in that the relative abundances of the two dominant phylum-level bacteria, the *Bacteroidetes* and the *Firmicutes*, are significantly changed between obese and lean human volunteers [57]. In an asthma mouse model, we previously reported that the gut microbiome directly contributed to increasing ozone-induced airway hyper-responsiveness and neutrophilic airway inflammation [25,58]. Unfortunately, there are insufficient data about the specific association between obesity-induced severe asthma and the gut microbiome. However, body weight reduction by bariatric surgery is associated with the improvement of asthma pathophysiology and increased *Akkermansia muciniphila* in the gut [29,59,60]. These data remind us of the possibility of a mechanistic basis of obesity-induced severe asthma via the gut microbiome. Given these findings, focusing on the gut microbiome as a treatment target in the present study is consistent with the published data and could have an impact on the unmet needs in asthma with obesity.

Future prospects for gut-microbiome-targeted therapy are mainly considered to include fecal microbiota transplantation (FMT), prebiotics, and probiotics [23]. Indeed, the effect of FMT is widely recognized in patients with gastrointestinal disorders, including Clostridium difficile infection and inflammatory bowel diseases [61,62]. Prebiotics that affect the gut microbiome by dietary supplementation, such as dietary fiber, have potential to attenuate allergic and non-allergic airway responses in vivo [25,26,63]. Further, probiotics involving the administration of beneficial and specific taxa have been increasingly clarified, and *Akkermansia muciniphila*, *Turicibacter*, and *Lactobacillus* are the candidates related to asthma pathophysiology in vivo and in humans [23,24]. Unfortunately, we still do not have consistent clinical data associated with gut-microbiome-targeted therapies for severe asthma, regardless of BMI. Therefore, the focus is on the prudent use of antibiotics such as macrolides in the present study. Indeed, macrolides are recognized to have anti-inflammatory effects along with altering bacteria and improving asthma control, as well as suppressing sputum inflammatory cytokines [64]. We also reported that macrolides attenuate allergen-induced airway responses, especially those driven by type 2 and non-type 2 inflammation [27,28]. According to these data supported by the AMAZES study [36], the present study will contribute to exploring new therapeutic drugs for obesity-induced severe asthma as an unmet need in the current clinical setting. Notably, induction of antibiotic-resistant microbes would be taken into consideration because the present study plans to involve long-term administration of azithromycin. A sub-analysis of the AMAZES study showed that several genes related to antibiotic resistance were increased from sputum DNA [53]. We do not know the impact of antibiotic-resistant microbe induction in the present study because the participants and intervention dose of azithromycin are different compared to the AMAZES study. Thus, the focus will be on the analysis of genes related to antibiotic resistance.

The limitations of the present study are that there are no control arms of lean subjects and placebo. The phenotypes of severe asthma in lean and obese subjects are different, and standardization of inflammatory and background characteristics of these two groups would be difficult given the need for an increased sample size caused by the huge standard deviation. Furthermore, there is no placebo group because of the gut microbiome diversity of individuals, as mentioned in the methods, even though triggers of asthma exacerbation and other factors associated with gut microbiome changes might not be standardized between before and after the azithromycin intervention. Thus, a single-arm intervention has been planned for the present study. Another limitation is that the inclusion criterion of 20–75 years of age is a wide range, which might affect the results of the metabolomics analysis.

